## Abstract

**Background:**

In general, urinary and faecal incontinence is a multifaceted problem that is associated with increasing burdens for those affected, a massive impairment of quality of life and economic consequences. Incontinence is associated with a high level of shame, which in particular reduces the self-esteem of those being incontinent and leads to additional vulnerability. Those affected by incontinence often perceive incontinence and the care they receiveas humiliating, hence they can no longer control their own urination; nursing care and cleansing support then lead to additional dependency. People with incontinence in need of care not uncommonly experience a poor communication and many taboos surrounding the issue as well as the use of force when incontinence products are changed.

**Aims and methods:**

This RCT aims to validate the benefits of using a digital assistance system to optimise incontinence care and to enable statements concerning the effect of the assistance technology on nursing and social structures and processes as well as on the quality of life from the perspective of the person in need of care. In a two-arm, stratified, randomised, controlled interventional study, primarily incontinence-affected residents of four inpatient nursing facilities will be examined (*n* = 80). One intervention group will be equipped with a sensor-based digital assistance system, which will transmit care-related information to the nursing staff (via smartphone). The collected data will be compared to the data of the control group. Primary endpoints are falls occurring; secondary endpoints are quality of life and sleep, sleep disturbances and material consumption. In addition, nursing staff (*n* = 15–20) will be interviewed regarding the effects, experience, acceptance and satisfaction.

**Discussion:**

The RCT aims at the applicability and effect of assistance technologies on nursing structures and processes. It is assumed that, amongst other things, this technology may lead to a reduction of unnecessary checks and material changes, an improvement of life quality, an avoidance of sleep disturbances and thus an improvement of sleep quality as well as to a reduced risk of falling for people with incontinence in need of care. The further development of incontinence care systems is of social interest as this offers the prospect of improving the quality of care for nursing home residents with incontinence.

**Trail registration:**

Approval of the RCT is granted by the Ethics Committee at the University of Applied Sciences Neubrandenburg (Reg.-Nr.: HSNB/190/22). This RCT is registered at the German Clinical Trials Register on July 8^th^, 2022, under the identification number DRKS00029635.

## Background

Incontinence refers to the body’s inability to retain and release urine (urinary incontinence) or faeces (faecal incontinence) in a controlled manner, resulting in an involuntary outflow. Experts estimate that between six and eight million people in Germany are affected by urinary incontinence and about four million are affected by faecal incontinence[1–3]. The exact prevalence of urinary and faecal incontinence is difficult to determine due to the different care settings (inpatient and outpatient) and data collection methods. Incontinence is often associated with further health problems such as dermatitis, falls, reduced daily activity, longer hospitalisations and higher mortality, whereby the overall quality of life of those affected is severely effected [4–7]. In addition, individuals affected by incontinence often experience psychological impairments such as a lack of dignity [8] because they can no longer control their own urination and defecation; care and cleansing support then lead to additional dependency [9]. If support is needed as part of care, those affected not uncommonly experience a poor communication and taboos concerning the issue as part of the everyday routine nursing care and even the use of violence during the change of incontinence material [10]. As the prevalence of incontinence increases with age this is predominantly a problem for long-term care [11]. It is estimated that approximately 80.4% of the individuals in long-term care are affected [1], and incontinence is most prevalent in individuals with increased care needs [12, 13]. If individuals are no longer able to express for themselves that incontinence products need to be changed, the nursing staff make these decisions. Whereby this leads to unnecessary controls of incontinence material, which are however often unavoidable and are accompanied by a disturbance of the person in need of care. In particular, nightly changes of incontinence materials have a negative impact on those affected, as additional sleep interruptions further reduce the already low quality of sleep [14]. The often unnecessary checks and changes of incontinence materials also have economic consequences. When calculating these effects, direct (e.g. costs for incontinence materials), indirect (e.g., loss of resources) and intangible costs (e.g. reduction in quality of life, restrictions on individual freedom) are differentiated, with direct costs being the simplest to calculate. A study conducted in 2007 analysed that the direct costs of urinary incontinence in Germany amounts to approximately €396 million. 70% of these costs (€277 million) are attributed to women and 30% (€118.6 million) are attributed to men. [15]. The direct costs of incontinence care are thus comparable to those of other chronic diseases such as dementia and diabetes [16, 17]. The indirect and intangible costs have not been scientifically evaluated yet but are estimated to be higher than the direct costs. Since the costs are significantly related to the severity of the incontinence as well as to the age and degree of care required by the affected individuals, the demographic change, amongst other factors, ensures that the costs will double in the next 50 years in Germany [18]. Despite the high prevalence of incontinence in long-term care [19], few international and national studies can be identified to date that adopt a nursing science perspective, revealing a research gap. Most studies focus on specific diseases and medical parameters but neglect nursing aspects, or they focus on physiological endpoints such as the effects of pelvic floor muscle and bladder function training (e.g. [20–24]. Studies with technical interventions in the field of incontinence are scarce and, if available, they focus tightly on medical parameters [25] or their results cannot be transferred to the primary target group of long-term care residents [26, 27]. Up to now there are only a few studies focusing on nursing parameters [among others, [27, 28]. Studies on the use of digital assistance systems in incontinence care with people in need of care that investigate the consequences on quality of life and sleep as well as the benefits of the technology on the quality of care overall have not been conducted yet. However, the combination of sensor technology with technical assistance systems in the field of incontinence care has made a significant progress in the past few years. (e.g. the system from AssistMe GmbH).

Routine visual inspections of care recipients' incontinence products are currently performed as standard practice in both outpatient and inpatient settings. This procedure significantly compromises a variety of aspects such as hygiene, ethics, the structure of daily life and work efficiency. A digital, sensor-based assistance system could replace visual checks in both outpatient and inpatient settings and improve the quality of incontinence care for both those in need of care as well as for nursing staff. Although the benefits of digital assistance systems in the field of incontinence care are promising, primarily the users (e.g. family caregivers, nursing staff) need to be convinced. Technical aids and digital assistance systems often lead to scepticism among nursing staff, this manifests itself in misunderstandings, worries and fears, a lack of information and insecurities concerning data usage [29]. This skepticism could be countered by letting nursing staff experience the benefits of these systems (e.g., improvement of incontinence care, avoidance of unnecessary changes) and by creating a familiarity with the assistance system among all participants. The latter is particularly the case when users are involved in the development of technical innovations. This also reduces the risk that technical aids are developed "parallel" to the care process [29]. Studies on this topic have not been conducted yet.

## Objectives and questions

This RCT aims to validate the benefits of using a digital assistance system to optimise incontinence care and to enable statements concerning the effect of assistance technology on nursing and social structures and processes as well as on the quality of life from the perspective of individuals in need of care. Answers are to be found in particular to the following questions:What are the benefits of planned assistance technologies for incontinent care recipients?Can assistance technologies reduce falls and improve quality of life as well as quality of sleep of incontinent individuals?What effects does the assistance technology have on existing structures and care processes in long-term care?How can implementation in nursing practice be organized and what kind of logistical measures are required for usage in long-term care (such as information materials, training of nursing staff, maintenance and care of the technical aids to ensure the required accuracy and reliability, procurement/disposal)? How can the technology be incorporated into routine processes in long-term care?In terms of economic perspectives, what results does a measurement or prognosis of success provide to potential users of assistance technologies?How can a sustainable utilisation of the technologies be assured?

In the long term this project aims to contribute to new quality-assured modes of care in nursing practice.

## Methods and design

This RCT is based on a mixed-methods approach and consists of a quantitative and a qualitative method strand, which are to be arranged in a parallel design to each other, allowing an integrative presentation of the results. The focus is on individuals requiring care in inpatient nursing facilities (primary target group) and on nursing staff (secondary target group). The approach selected intends to generate a comprehensive understanding concerning the use of digital assistance systems for incontinence care, which represents the different perspectives of the target groups and captures the complexity of the research subject as a whole.

This study protocol is guided by the SPIRIT Statement [30].

Concerning the *primary target group of care recipients*, a two-arm, stratified and randomised, controlled interventional study is selected for the study design (RCT). Participants will be assigned to the intervention group (IG, equipped with a digital assist system) and control group (CG, not equipped with a digital assist system) study arms, and the assignment of study participants to arms will be randomized. To ensure a homogeneous distribution regarding the prognostic factor of impaired abilities to the IG and CG, a simple disproportionate stratification will be performed prior to the randomisation. This will ensure that a valid interpretation on the efficacy of the intervention is possible. Other advantages of this approach refer to a reduced probability of an α and/or β error when interpreting the results, furthermore the statistical validity of the results with a comparably low participant number is increased, and interim analyses are simplified [31–33]. The participants will be stratified using the Mini Mental Status Examination (MMSE). On the basis of the points achieved in the questionnaire, care recipients will be allocated to the subgroups “cognitively impaired” (points < 18) and “not cognitively impaired” (points > 18). In previous studies, the use of self-reported scales up to an MMSE point value of > 10 proved to be appropriate [including [34, 35]. However, in the study implementation, the results of the MMSE are used for stratification from a score of > 18. As a result, the RCT is based on the original values of the instrument [36]. Participants that have been identified as cognitively impaired by the assessment results of the MMSE (score 0 to 18) will be reported back: both nursing staff and participants affected shall estimate as objectively as possible whether the benefit of self-reported scales is appropriate. Participants who score below 18 on the MMSE or for whom assessment feedback argues against self-assessment scales will be administered assessments as third-party assessment scales.. After stratification, the participants of the two subgroups will be randomized individually to the two study arms IG or CG (see Fig. 1).

**Fig. 1 Fig1:**
[figure not shown]
Flow chart concerning the primary target group [37]

Concerning the *secondary target group of nursing staff*, a single-armed observational study design is selected. All participants will be surveyed both quantitatively and qualitatively at four time points.

When randomizing both groups, additional attention will be paid to the individual framework conditions of the participating inpatient care facilities and they will be appropriately responded to.

## Methods

Within the framework of the RCT, care recipients affected by incontinence and their responsible nursing staff will be monitored in four selected inpatient care facilities in Berlin and Brandenburg over a system test period of four months.

### Inclusion criteria

#### Primary target group

To consider the different comorbidities of the primary target group and to be able to realistically assess the benefits of the digital assistance system, the inclusion criteria were defined relatively broadly. Individuals included in the RCT:have a moderate to severe incontinence (degree of severity ≥ 2, urinary or urinary and faecal incontinence) andhave given their written informed consent to participate in the RCT after receiving information and clarification. If individuals are not able to consent to study participation by themself due to cognitive impairments, their family caregivers or legal guardians may provide consent.

The severity of incontinence is determined by the consumption of incontinence material per person in need of care as recorded in the care documentation.

Due to the multifaceted occurrence of incontinence, other factors such as cognitive ability, mobility as well as the degree of care of the person affected do not play a role as criteria for study participation. Individuals who are cognitively impaired as well as not impaired; who are mobile as well as immobile; and who have a high or low level of care will be included in the RCT.

#### Secondary target group

Since nursing staff is to incorporate and evaluate the digital assistance system as part of their professional activities, only the nursing staff responsible for incontinence care is included in the study. By doing so, differentiated statements about the system can be voiced by the nursing staff. Ideally, the included nursing staff is also responsible for participants in the control group, enabling them to identify and describe any changes concerning nursing care with an even greater nuance. Furthermore, a written consent to participate in the study after being informed and educated is necessary. In addition, nursing staff with similar as well as different characteristics such as professional experience, age and gender is included. Thereby, the individuals should differ as minimally and maximally as possible. This contrastive sampling procedure intendeds to reflect the heterogeneity of the research subject through the selection of individuals to be interviewed [38].

### Exclusion criteria and dropout management

#### Exclusion criteria of the primary target group

In order to include as many individuals as possible in the RCT, the exclusion criteria will be defined relatively narrow.

Individuals will be excluded from the RCT if:they or their responsible nursing staff decline to participate in the study and therefore do not sign the written declaration of informed consent, and ifthey only have a mild form of incontinence (degree of severity 1, urinary or urinary and faecal incontinence).

#### Exclusion criteria of the secondary target group

Nursing staff will only be excluded from the study if they do not agree in writing to participate and/or if they are not responsible for the incontinence care of the primary target group.

#### Dropout criteria of the primary target group

Individuals may withdraw from their study participation at any time. They or their responsible nursing staff can revoke their consent to participate in writing. Likewise, they are automatically excluded from the RCT if they die during the intervention.

A deterioration in their health does not necessarily lead to exclusion from the RCT. Those affected are only excluded from further study events if the deterioration is due to compelling medical and/or nursing reasons requiring a termination of their participation in the study.

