### Endpoints

#### Endpoints of the primary target group (care recipients with urinary and faecal incontinence)

Occurring falls represent the primary endpoint of the RCT. Secondary endpoints include cognitive ability, quality of life, sleep quality and disruptions of sleep, incontinence material consumption and general health.

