#### Endpoints of the secondary target group (nursing staff)

The secondary target group will be surveyed by means of interviews regarding the acceptance, experience and perceived effects of the digital assistance systems and the resulting changes to their work processes (secondary endpoints). This qualitative data collection captures the important perspectives of nursing staff and nursing management.

In addition, the nursing staff will also be surveyed quantitatively about their subjective attitude toward the use of technology in their professional context and concnerning the use of the digital assistance system in particular. The subscales of the questionnaire to measure the affinity for technology scale (TA-EG) are used as guidance. The TA-EG consists of 19 items and four scales and has been adequately reviewed in terms of its validity and reliability. Due to its scope, it will be used in a shortened form in the study and adapted to the specific core of the intervention. The modified questionnaire was tested in pretests with regard to comprehensibility, practicability and temporal scope. Subsequently, editorial changes were incorporated (see Table 1).

**Table 1 Tab1:** Endpoints and measurement tools for the primary target group

Primary endpoints	Measurement tools
Incipient falls	**STRATIFY instrument** (St. Thomas’s risk assessment tool in falling elderly inpatients) [39] • Includes five items / risk factors • Confirmed validity and reliability [40] • Quantitative method, third-party assessment **Tinetti Test** [41] • Includes 17 items • Confirmed validity and reliability [42] • Quantitative method, third-party assessment **Extrinsic and intrinsic risk factors** for the residents • based on and correlating with the national expert standard on incontinence of the German Network for quality standards in care-giving (DNQP) [11] **Analysis of fall records** • Documentation through the nursing facility is mandatory • Provides important information about occurring falls and possible consequences of falls
**Secondary endpoints**	**Measurement tools**
Cognitive ability	**Mini Mental Status Examination (MMSE)** [36] • Consists of five categories with a total of 11 items • Confirmed validity and reliability • Used for stratification • Quantitative method, self-reported scale

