### Measurement period

In the context of the intervention study, the incontinence-affected individuals included are accompanied over a system test period of four months. The measurements will take place exclusively in the respective inpatient care facility. For better supervision by the study management, the measurements should be carried out in a maximum of two facilities in parallel during the project period. The measurements will be carried out exclusively by the study staff of the University of Applied Sciences Neubrandenburg.

A total of seven measurement points are planned for the participants of the primary target group. One measurement will take place at the start (t0) and one at the end (t6) of the four-month study period. Between these two points (t0 and t6), the quantitative surveys will be conducted every three weeks (t1, t2, t3, t4, t5). If necessary, when taking the measurements, the study staff of the Neubrandenburg University of Applied Sciences may be assisted by the nursing staff of the relevant inpatient nursing facility (e.g. if a participant has a greater cognitive impairment).

Four measurement points are planned for the individuals of the secondary target group. One measurement will take place at the beginning (t0) and one at the end (t3) of the four-month study period. In the meantime, the qualitative and quantitative surveys will take place every six weeks (t1, t2) (see Fig. 3 and Table 2).

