### Recruitment

#### Primary target group

The recruitment procedure is divided into two phases: 1) The study staff of the Neubrandenburg University of Applied Sciences and those responsible from AssistMe will visit the participating inpatient nursing facilities. In an open event all residents of the facility who are interested will be informed about the RCT (including the aims of the study, procedure and the intervention). This is meant as opportunity to ask questions to the persons responsible for the RCT. This shall emphasise the absolute voluntary nature of study participation. 2) If the residents or their family caregivers/legal guardians indicate interest in participating in the study, they inform the responsible nursing staff in the facility. The nursing staff consolidate the interested parties and forward their names to the study staff at the Neubrandenburg University of Applied Sciences. The study staff then visits the interested parties again. In a conversation, they will be again informed in detail about the RCT as well as the intervention. In addition, the inclusion and exclusion criteria will be checked. Residents who meet the eligibility criteria and who would like to participate in the RCT are then examined regarding their cognitive performance using the Mini Mental Status Examination (MMSE). Depending on their score, they are assigned to the respective strata "cognitively impaired" or "not cognitively impaired." Subsequently, both subgroups are randomized individually into the intervention and control group.

Should individuals in the primary target group drop out of the RCT prematurely (e.g., due to compelling medical or nursing reasons), new particpipants will be recruited and included if they meet the inclusion criteria. This post-recruitment is foreseen up to a maximum of two months after the start of the system test period.

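### Termination on medical or nursing grounds, which may follow a serious fall, also ends collection of falls, the primary endpoint, although the facility must document falls and consent has not been revoked

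*Protocol article*

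**What the plan says.** The endpoint section is plain: "Occurring falls represent the primary endpoint of the RCT". Follow-up is fixed in the section Measurement period: "the incontinence-affected individuals included are accompanied over a system test period of four months". Table 2 schedules the analysis of fall records at every visit from t0 to t6. Table 1 says of those records: "Documentation through the nursing facility is mandatory".

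The dropout section for residents starts from a permissive rule: "A deterioration in their health does not necessarily lead to exclusion from the RCT". It then sets the exception under which study participation ends: "Those affected are only excluded from further study events if the deterioration is due to compelling medical and/or nursing reasons requiring a termination of their". Revoked consent and death are listed there as separate routes out.

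The Recruitment section for residents treats the exception as a full dropout. It opens with "Should individuals in the primary target group drop out of the RCT prematurely (e.g., due to compelling medical or nursing reasons" and goes on to provide for new participants. It adds: "This post-recruitment is foreseen up to a maximum of two months after the start of the system test period".

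No section says that fall records are still extracted after such a termination, and none sets fall-related deterioration apart. The section Data management requires removal of data only when consent is withdrawn.

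**The concern.** Falls are both the outcome and a plausible cause of the deterioration that ends participation. Where that happens, follow-up for the primary endpoint stops because of the primary endpoint. If one arm falls more, it loses more follow-up, and a comparison of fall counts is pulled towards no difference.

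The loss can also differ between arms for other reasons. The section Blinding states that residents, nursing staff, the system provider and study staff all know the allocation, and only one arm has a system to stop. The judgement that participation must end is therefore made with the arm known, and the resulting bias could run in either direction.

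The loss is avoidable. The facility's records exist whether or not the study reads them, and consent has not been revoked. An analysis plan cannot make up for falls that the study never extracted, so this is more than a detail left to a later document.

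**Working it through.** **1. The plan's own figure.** Inputs from the section Power calculation: means 2.22 and 1.65, SD 0.84, significance level 0.05, power 80%, 34 per group, about 15% dropout, 80 in total. The section does not say which arm 1.65 belongs to, or whether the test is two-sided.
- Read as 2.22 − 1.65 = 0.57, two-sided: n = 2 × (1.960 + 0.842)² × 0.84² / 0.57² = 34.1 per group. This is 35 rounded up, against 34 stated.
- 68 / 0.85 = 80. The stated total reproduces.
- Read as 1.65 − 1.13 = 0.52, the result is 41 per group two-sided or 33 one-sided. The 0.57 reading is used below.

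**2. What early exclusion does to raw counts.** Assumptions, none of them in the document:
- falls are Poisson with mean m over the four months;
- each fall leads to exclusion with probability p;
- counting stops after that fall;
- the resident would otherwise have kept falling at the same rate.

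Then expected counted falls = (1 − e^(−pm)) / p, and the share excluded = 1 − e^(−pm).

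| p | Control counted | Intervention counted | Difference | Excluded, control / intervention | Average excluded |
|---|---|---|---|---|---|
| 0 | 2.220 | 1.650 | 0.570 | 0% / 0% | 0% |
| 5% | 2.101 | 1.584 | 0.517 | 10.5% / 7.9% | 9.2% |
| 10% | 1.991 | 1.521 | 0.470 | 19.9% / 15.2% | 17.6% |
| 20% | 1.793 | 1.405 | 0.387 | 35.9% / 28.1% | 32.0% |

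A simulation with 1,000,000 residents per arm agreed with the formula. With means 1.65 and 1.13, the difference goes from 0.52 to 0.485 at p = 5%.

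**3. Against the dropout allowance.** The plan allows about 15% for all causes. The rows for 10% and 20% exceed this through fall-related exclusion alone, so they do not fit the plan's own expectation. At 5%, 15 − 9.2 = 5.8 percentage points remain for death, withdrawal and everything else.

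**4. If falls become rarer after exclusion.** At p = 5% the uncounted falls are 2.220 − 2.101 = 0.119 (control) and 1.650 − 1.584 = 0.066 (intervention), a gap of 0.053. If the fall rate after exclusion is r times the earlier rate, continued extraction recovers r × 0.053 of the difference: 0.053 at r = 1, about 0.026 at r = 0.5, nothing at r = 0.

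**5. If falls are analysed per time at risk.** At a constant rate, the expected time at risk at p = 5% is 2.101 / 2.22 = 0.946 of the four months (control) and 1.584 / 1.65 = 0.960 (intervention). Dividing counted falls by these fractions returns 2.22 and 1.65, so the shrinkage disappears. It does not fully disappear if frailer residents both fall more and leave sooner.

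**The case against.** The case against has real weight, mostly against stronger readings.

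- A reader might infer that any resident who deteriorates is excluded. The dropout section says the opposite as its general rule and limits exclusion to cases where participation has to end.
- A reader might infer that stopping the system means leaving the study. The dropout section does not mention the system, and Possible harms lets intervention residents move to standard care without calling that dropout.
- A bed-bound resident after a fracture is a tempting example. But the inclusion criteria admit immobile residents and any level of care, so becoming immobile or needing more care is not in itself a stated reason to terminate. Such a resident might also hardly fall again, in which case little is lost.
- A reader might take 9% to 32% of the effect as lost. That range rests on an assumed p, an unchanged fall rate, raw counts, and treating the cited trial's means as four-month means. Its upper part conflicts with the dropout allowance.
- A reader might suspect that harm from the system is being hidden. The documents give no evidence of this, and Possible harms says that the system adds to usual care and does not replace it.
- The section Statistical methods names regression and multilevel analysis without tying a model to falls. A full plan could specify a rate per time at risk.

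These points limit the size. They do not answer the core point: as written, participation and its measurements end, fall records are among those measurements, and nothing provides for extracting them afterwards.

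**Conclusion.** The point holds in a limited form. A termination on medical or nursing grounds, which may follow a serious fall, ends follow-up for the primary endpoint and makes the resident a replaceable dropout, although the data source continues and consent has not been revoked. The loss may be unequal between unblinded arms.

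The documents give no figure for its size. The one illustrated case that fits the dropout allowance (5% chance per fall) takes the counted difference from 0.57 to 0.52, about 9% of it. This depends on Poisson falls, four-month means, raw counts and an unchanged rate after exclusion. The loss is near zero if excluded residents would seldom fall again, and much smaller with a rate per time at risk. Continued records are available only while the resident lives in the facility. This is a worthwhile low-cost improvement, not a flaw that invalidates the trial. Whether and when clinical grounds should end participation is not judged here.

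**What to change.** Leave the clinical termination criterion as it stands and separate it from data collection. Add to the dropout section that:

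- for every randomised resident whose consent stands, facility fall records are extracted to the end of the four months, or to death or leaving the facility;
- time at risk is recorded;
- the resident is analysed in the randomised arm, whether or not a replacement is recruited.

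The cost is a short addition to the text and a little more extraction of records the facility already keeps. The downside is that time off the system is included for some intervention residents, which slightly dilutes the effect.
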